# STUDY DESIGN

## Overview

This is a double-blind randomized placebo-controlled clinical trial to examine the long-term efficacy of a short classroom-based teaching session about air pollution on the understanding and behavioral choices of middle school students, The study will be using a repeated measure design. A one-hour interactive script-based evidence-supported teaching curriculum about air pollution will be developed and its effects on climate change and human health.

Furthermore, to assess the effect of the teaching session, we developed a survey questionnaire with two topic domains to evaluate the understanding and future behavioral choices of the participating adolescents towards air pollution. We also developed a one-hour teaching session about health benefits of vaccination to be used as the control teaching session.

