# CRITERIA FOR EVALUATION

## Efficacy Endpoints

The study primary and secondary outcomes are listed below:

- The primary outcome of the study is the questionnaire behavioral domain score.
- The secondary outcomes are the questionnaire total and understanding domain score.

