**Visit 1**

- Questionnaire: The enrolled students will complete a survey (15 multiple-choice questions; five targeting understanding (score range 5-20); ten targeting behavioral choices (score range 10-38)) designed to evaluate their understanding and predict their future behavior towards air pollution immediately before the intervention.
- Teaching session: participants will be given a one-hour script-based teaching on either the effects of air pollution on lung health (intervention group) or the role of vaccination in public health (control group). The teaching session also includes offering students to breathe through a straw and also undergo spirometry.
- Questionnaire: The enrolled students will complete the same survey immediately after the intervention.

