### Dependent Variables

- Behavior domain score (primary outcome).
- Total domain score (secondary outcome).
- Understanding domain score (secondary outcome)

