## Statistical Models

- Paired t-test comparison of pre versus post teaching session.
- Linear regression modeling analysis will be performed to compare the scores and change in them between the intervention and control group with adjustment for covariates including age, sex, race, ethnicity, income level, and assigned classrooms as appropriate.
- Multivariate generalized estimating equation regression analysis will be performed to determine whether there is an incremental effect from “time” on scores and change in scores with adjustment for covariates including age, sex, race, ethnicity, income level, and assigned classrooms as appropriate.

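### The primary behavior score has no time point or fixed form, so the one test the trial is sized for is not identified, and the GEE's stated target is time, which does not test the teaching effect

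*Protocol*

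**What the plan says.** Protocol 7.1 (Overview) describes a repeated-measures trial "to examine the long-term efficacy of a short classroom-based teaching session". Section 8.1 states: "The primary outcome of the study is the questionnaire behavioral domain score". Section 13.2.2 lists the same score as primary. Neither gives a visit.

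Under 12.2, the survey is taken before teaching and then four times after it. At Visit 1, "The enrolled students will complete the same survey immediately after the intervention". Visits 2, 3 and 4 repeat it at about 3, 6 and 12 months.

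Section 13.1 sizes the trial for a t-test on change in score, two-sided at 0.05, again without a visit.

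Section 13.4 lists three analyses and calls none of them primary:

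1. "Paired t-test comparison of pre versus post teaching session".
2. Linear regression to "compare the scores and change in them between the intervention and control group", adjusted for covariates.
3. A GEE to "determine whether there is an incremental effect from “time” on scores and change in scores", adjusted for the same covariates.

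**The concern.** There are two linked problems.

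**The deciding test is not named.** Four post-teaching surveys and two outcome forms (score or change) all fit the definition of the primary outcome. A difference at the immediate post-test could be reported as the primary result, although it says nothing about the long-term efficacy that section 7.1 sets as the aim. Naming the time point of the primary endpoint belongs in a protocol and is not a detail to leave for the SAP.

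**The longitudinal model is pointed at the wrong term.** Whether a teaching effect appears, persists or fades is a question about the difference between arms at each survey. A time effect common to both arms reflects maturation, repeat testing or outside events. The regression item in 13.4 states a between-arm purpose, but the GEE item states only a time purpose.

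**Working it through.** **1. The plan's own sample size.** Inputs from 13.1: difference 10%, SD of change 40%, two-sided alpha 0.05, power 80%.

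n per group = 2 × (1.960 + 0.842)² × (40/10)² = 2 × 7.851 × 16 = 251.2, rounded up to 252, so 504 in total. This reproduces the stated figure, and power at 252 per group is 80.1%. A paired t-test on the same inputs would need only about 128 pairs. The figure therefore belongs to one two-sample comparison of change at 5%. The Protocol does not say at which visit that comparison is made.

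**2. Room for choice among visits.** Suppose any of the four post-teaching between-arm tests, each at 0.05, could be called primary. If the tests were independent, the chance of at least one false positive would be 1 − 0.95⁴ = 18.5%. Repeated scores are correlated, but the Protocol gives no correlation, so a range is assumed (equal correlation between all pairs, simulated normal test statistics):

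| Assumed correlation | P(at least one p<0.05, no effect) |
|---|---|
| 0.3 | 17.3% |
| 0.5 | 15.6% |
| 0.6 | 14.4% |
| 0.7 | 13.1% |
| 0.8 | 11.4% |
| 0.9 | 9.4% |

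Counting only the 3-, 6- and 12-month visits, the figure is 14.3% if independent, and 13.5% to 8.4% for correlation 0.3 to 0.9. The choice between score and change is not counted here.

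Keeping all four open under a Bonferroni correction would cost power: 252 per group gives 62.1% per test, and 357 per group would be needed for 80%. Naming one contrast leaves the planned 80.1% unchanged.

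**3. What a time term can show.** Take equal arms and an invented change from 3 to 12 months:

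- Intervention falls 2 points, control is flat: pooled time effect (−2 + 0)/2 = −1.
- Both arms fall 1 point, no teaching effect: (−1 − 1)/2 = −1.

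The time effect is the same in both. The change in the arm difference is −2 in the first and 0 in the second.

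**4. The same point with arm in the model.** A GEE was simulated with 480 students (600 less 20%), one survey before and three after teaching, exchangeable correlation 0.5 (assumed), and 200 runs per scenario. Time was coded as before versus after. The shift of 0.25 SD matches 10/40 from 13.1, because at correlation 0.5 the variance of change, 2 × (1 − 0.5) = 1, equals that of the score. The time column comes from a model with time and arm, and the last column from the model that adds arm-by-time.

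| Scenario | Time significant | Arm-by-time significant |
|---|---|---|
| No shift, no teaching effect | 5.0% | 6.0% |
| Shift of 0.25 SD in both arms, no teaching effect | 100% | 5.5% |
| No common shift, teaching effect 0.25 SD | 90% | 92% |

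The time term is nearly always significant in both the second and third rows, so it cannot tell them apart. Arm-by-time stays near 5% without a teaching effect (simulation error about √(0.05 × 0.95/200) = 1.5 percentage points) and detects the effect when there is one.

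**The case against.** The strongest reply is that the plan does contain a sound test. Students are randomized within classrooms (section 10), and the linear regression in 13.4 compares the arms with covariate adjustment. At any given visit that is a valid test of the teaching effect, and it would separate the two scenarios in step 3. This stands. A reader might infer that the Protocol has no valid between-arm test; the documents do not support that. What is missing is which visit and which outcome form that test uses when it decides the trial.

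Second, a reader might infer that arm has been left out of the GEE, since it is not among the listed adjustments. That does not follow. Section 13.2.1 makes the teaching session the independent variable, and the opening of section 13 says regression will examine whether that variable predicts the outcome. Arm is not a covariate in this Protocol, so its absence from the covariate list proves nothing, and the SAP, which is not shown, may give the full model. The narrower point survives: the target stated in the Protocol is time, and step 4 shows that having arm in the model does not turn a time term into a test of the teaching effect.

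Third, the Protocol does not plan four tests at 5% with the best one winning; 13.1 describes a single test. The 11% to 16% should not be read as the planned type I error. It depends on assumed correlations and on a visit being chosen after the data are seen.

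Finally, 12 months is not the only defensible horizon. The exclusion for moving away looks 6 months ahead (9.5), which could suggest a different one.

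**Conclusion.** The concern holds in this form. No section gives the primary behavior score a time point, and 13.4 leaves its form open between score and change, so the single 5% test behind the 504 students is not identified. The only explicitly longitudinal model has a stated target that cannot show whether the teaching effect appears or lasts.

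The room for selective reporting is about 11% to 16% against a nominal 5%, for four between-arm tests with assumed correlation 0.8 to 0.5; it remains above 5% across every correlation examined. The statement about the time term rests on what such a term estimates; the simulation only illustrates it under assumed correlation and shift. The design, visits and sample size are not in question here, and the between-arm regression is usable once it is pinned down.

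**What to change.** 1. In 8.1, 13.1 and 13.2.2, name one visit and one outcome form for the primary between-arm contrast in the behavior domain score, adjusted for baseline behavior score. Twelve months is one option consistent with the stated long-term aim; the choice is the sponsor's and should be justified in a sentence. With baseline in a linear model, score and change at that visit give the same arm coefficient, so the choice of form then carries no practical risk.
2. In 13.4, say which model delivers that contrast.
3. Restate the GEE as behavior score at the four post-teaching surveys on arm, categorical survey time, arm-by-time, baseline behavior score and the covariates already listed. Report the arm difference at each survey, and use arm-by-time to judge whether the effect changes over time.
4. Label the paired t-test and the arm differences at the other visits as secondary.

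The cost is Protocol wording and a few model terms. Sample size, visits and procedures stay as they are. The real concession is that the other time points can no longer carry the primary claim.

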## Interim Analysis

The progress of the trial will be monitored as detailed in Data Safety and Monitoring Plan. An interim analysis to evaluate the reliability and validity of the study instrument, the survey questionnaire will be performed.

## Medical Monitoring

Internally, the investigator and co-investigator will perform the quarterly safety reviews. Externally, a Data Safety and Monitoring Board (DSMB) has been created to evaluate the study with respect to the following:

- Participant safety, burden, confidentiality, and any other matter pertaining to protection of study subjects.
- Quality control, including follow-up for events, and Study productivity in terms of significant research results in addressing the primary study aims.

The DSMB members will include two senior investigators not directly involved with the study.

# TRIAL REGULATORY MATTERS

The University of California San Francisco (UCSF) Institutional Review Board (IRB) and the San Francisco Veterans Affairs Health Care System (SFVAHCS) Committee on Research and Development approved the study protocols. The study is registered with the United States (U.S.) National Library of Medicine (Behavioral Research of Environment and Air Pollution Through Education (BREATHE) study; ClinicalTrials.gov identifier NCT02471872).

# ADVERSE EXPERIENCE REPORTING AND DOCUMENTATION

This study is a category 7 low risk behavioral research, and it will be performed under no greater than minimum risk (45 CFR 46.404,21 CFR 50.51).

## Risk/Benefit Assessment

The risks of this study are minimal compared to potential benefits it holds for public health, both locally and globally. Air pollution is a significant and escalating problem affecting numerous countries. The findings of this study can inform the development of future interventions aimed at promoting environmental awareness and behavior change among adolescents and ultimately contribute to reduction of the global public health burden of air pollution.

# QUESTIONNAIRE SCORING
